To ensure maximal effectiveness and safety of exercise interventions [26, 27], experts in the field of cardiovascular health are regularly updating the guidelines containing recommendations for PA of patients with CVD. Between 2004 and 2006, the European Society of Cardiology (ESC) published miniseries of position papers that summarized specific recommendations for PA of patients by pathology [28–33]. A three-part miniseries published by the ESC in 2012 was describing the importance of PA and exercise modalities in the management of cardiovascular health. This time, exercise recommendations were dedicated for the general population [34], individuals with cardiovascular risk factors [35], and individuals with CVD [36]. The latest upgrade of ESC’s guidelines for PA was done in the year 2016 [37].

Despite the strong emphasis on regular exercise during lifestyle counselling [38], in the EUROASPIRE IV (European Society of Cardiology survey on the lifestyle, risk factor and therapeutic management of coronary patients), more than 59% of the interviewed patients reported little or no PA [39]. To clarify these conflicting observations, we need take to account the ecological factors [40], the quality of communication between care-providers and patients, [41, 42] and the patient’s skills to access, understand and use of disease-specific instructions and recommendations [43, 44]. The latter domain is also labelled as the patient’s health literacy (HL). The HL level influences the patient’s use of healthcare, quality of disease management and health risk behaviours [45] and reflects patient’s proactivity in attempting to utilize health literacy skills [43]. Sufficient HL is significantly associated with improved health outcomes with a lower cost of care [45], while HL inadequacies can compromise patient safety, worsen management of a disease and increase the incidence of health conditions requiring intense medical assistance or hospitalization [46]. In older adults, inadequate HL was significantly associated with poor implementation of PA recommendations [47]. For improvement of patient’s accessibility and applicability of health-related knowledge in real life, we need to emerge that patients and health professionals cannot address these needs independently [48].

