### Primary outcome measures

The *primary outcome* is exercise recommendations adherence as assessed by agreement between the patients reported and the prescribed indices of exercise. The indices are type, duration, intensity and frequency of exercise. Patient-reported type, duration, intensity and frequency of exercise will be assessed using a short self-report questionnaire (Table 4), reflecting the construction and definition of exercise prescriptions generated by the EXPERT tool. The questionnaire will be filled with assistance of an investigatory team member and he will ask participants to report regularity on exercise over the last year and describe in detail the type, duration, intensity and frequency of exercise realized over the last 3 months. Exercise recommendations adherence will be determined as agreement between indices of exercise prescription delivered by EXPERT tool and self-reported indices of exercise performed in monitoring period (3 months). In the follow up assessment, the last section of the questionnaire will be dedicated on the general evaluation of PA behavioural change (by the question: “Have you registered a change in your PA behaviour during the last three months?”; with options for answer: “Definitely/Partially/Only limited change/Not at all”).

**Table 4 Tab4:** Measurement dimensions of exercise recommendations adherence and outcome variables

Measurement dimensions	Outcomes variables (independent data for last 3 months recall period)
Type of exercise	• Endurance training (walking, bicycling, swimming) • Strength training (free weight or resistance strength training, weightlifting) • Speed training (all short duration exercises with high intensity) • Anaerobic training (all exercises generating “lactate feelings”) • Sport games or mixed/other training
Duration of exercise (in one session)	• 0–10 min. • 10–20 min. • 20–30 min. • 30–45 min. • 45–60 min. • 60–90 min. • 90–120 min. • 121 and more min.
Intensity of exercise (typical intensity)	• Light Activity: an activity that does not cause you to ‘huff and puff’. • Moderate Activity: an activity that makes you breathe harder than normal, but only a little. • Vigorous Activity: an activity that makes you ‘huff and puff’.
Frequency of exercise (per week)	• Daily • 3–6 per week • 1–2 per week

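### The primary-outcome questionnaire (Table 4) has no accurate answer for patients who exercised less than weekly or not at all, and six of its duration boundaries fall in two bands

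*Protocol article*

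**What the plan says.** Under Primary outcome measures, the protocol article defines adherence as "agreement between indices of exercise prescription delivered by EXPERT tool and self-reported indices of exercise performed in monitoring period (3 months"). The indices are type, duration, intensity and frequency, and the patient's side of the comparison "will be assessed using a short self-report questionnaire (Table 4"). Table 4 prints these response options for the three-month recall period:

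- **Frequency:** "Daily • 3–6 per week • 1–2 per week".
- **Duration:** "0–10 min. • 10–20 min. • 20–30 min. • 30–45 min. • 45–60 min. • 60–90 min. • 90–120 min. • 121 and more min".
- **Intensity:** three levels, of which the lowest is "Light Activity: an activity that does not cause you to ‘huff and puff".
- **Type:** four named kinds of training, then "Sport games or mixed/other training".

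The same section mentions two items outside Table 4: how regularly the patient exercised over the past year, and, at follow-up, a four-level question on perceived change in activity. A team member helps the patient complete the form. Table 1 schedules it at baseline and at three months. The Background cites a survey of coronary patients in which "more than 59% of the interviewed patients reported little or no PA".

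**The concern.** When the outcome is agreement with an exercise prescription, the plainest form of non-adherence is to have done nothing. The printed options do not let the form record that cleanly. Nothing in the inclusion criteria requires patients to be active already, and the form is also used before any counselling, so such patients are to be expected at baseline and may well occur at three months.

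Two things could then happen. If the nearest option is ticked, an inactive patient is entered as exercising once or twice a week at some type and intensity. If the items are left empty, there is no reported value to set against the prescribed one, and the planned intra-class correlation needs both. Should inactivity differ between the arms, which is close to what the trial tests, either outcome would distort the comparison.

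The duration bands raise a smaller issue. Adjacent bands share endpoints at common session lengths, and no rule says which band takes the boundary value.

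**Working it through.** **1. Which patients lack an accurate answer (Table 4).**

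| Index | Nearest option to no exercise | Accurate for no exercise? | Accurate for less than weekly? |
|---|---|---|---|
| Type | mixed/other | no | yes |
| Intensity | light | no | yes |
| Frequency | 1–2 per week | no | no |
| Duration | 0–10 min | admits zero, but merged with up to 10 min | yes |

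A non-exerciser lacks an accurate answer on 3 of 4 indices. A less-than-weekly exerciser lacks one on 1 of 4.

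**2. Whether another instrument fills the gap.** The regularity item covers a year, not the three-month window. The change item asks about perceived change, not level; an inactive patient who stays inactive and an active one who stays active could give the same answer. The IPAQ-SF (Secondary outcome measures) recalls seven days and is aimed at activity other than exercise. None supplies the missing three-month value.

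**3. Duration boundaries.** Eight bands have seven internal boundaries. Listing whole minutes that satisfy two bands gives 10, 20, 30, 45, 60 and 90, which is six of seven. Only 120/121 is clean. A prescribed 30 minutes may be coded 20–30 while a reported 30 is coded 30–45: a false mismatch. A prescribed 30 and a reported 20 may both be coded 20–30: a match that depends only on the choice of band.

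**4. Sensitivity of power, if patients were lost.** This is illustration only, since the documents give no loss fraction. Inputs from Sample size: effect size 0.33, 80% power, two-sided α 0.05, 144 per group. (The same sentence also says 150, which is a separate matter.)

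The plan's figure first: n per group = 2(1.960 + 0.842)² / 0.33² ≈ 144.2, or 145 rounded up, so the stated 144 is reproduced.

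Power = Φ(0.33 × √(n/2) − 1.960), assuming equal loss in both arms and an unchanged effect size:

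| Assumed loss | n per group | Power |
|---|---|---|
| 0% | 144 | 80.0% |
| 10% | 144 × 0.90 = 129.6 | 75.7% |
| 20% | 144 × 0.80 = 115.2 | 70.7% |
| 30% | 144 × 0.70 = 100.8 | 64.9% |
| 40% | 144 × 0.60 = 86.4 | 58.3% |
| 59% | 144 × 0.41 = 59.0 | 43.4% |

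The last row is an outer limit, not an expectation. The cited 59% adds little activity to none. Table 4 accepts walking as endurance training and offers a light intensity, so many low-activity patients would find a fitting answer.

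**The case against.** Table 4 may not be the entire form. Its title speaks of dimensions and outcome variables, the text describes items it does not show, and the answer options of the regularity item are not given. A *no exercise* answer or skip rule could exist there. The form is completed with help, and one trained team member does all assessments, so that person could write in *none* and apply one boundary rule throughout. A prescription given as a range would also be less exposed to the overlap.

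This stands as a limit on the consequences: miscoding or loss is possible, not certain. It does not remove the defect. The text names Table 4 as the instrument, the printed options are the problem, and an analysis plan cannot recover an answer the form did not offer. The assessor is also unblinded and delivers the counselling (Randomization and allocation; Intervention; Monitoring), so unwritten discretion over a primary index is a weak safeguard.

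A reader might infer four stronger things that the documents do not support:

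- *That inactive patients leave the primary analysis.* Under Data analysis, restriction to patients without missing observations defines only the additional per-protocol analysis; the primary approach is intention-to-treat.
- *That ticking 1–2 per week always inflates adherence.* If indices are matched category by category, it does so on frequency only when the prescription is also 1–2 per week. Against a higher prescribed frequency it remains a mismatch.
- *That about six in ten patients have no answer.* The 59% does not separate little from no activity.
- *That overlapping bands must produce mismatches, or favour one arm.* They permit false matches and mismatches alike, and no direction between the arms is shown.

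**Conclusion.** The point holds as a defect in the response options printed for the primary outcome. Used as written, the form cannot accurately record absence of exercise on three of four indices, or less-than-weekly exercise on frequency. Duration does admit zero, but only merged with sessions of up to 10 minutes. The number of patients affected and the direction of any bias cannot be derived from the documents. The power figures are a sensitivity range resting on assumed, equal losses. The duration overlap, at six of seven internal boundaries, is real but secondary. The conclusion assumes that Table 4 shows the options as they appear on the form.

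**What to change.** Revise the form, preferably before first enrolment:

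- Add *none* and *less than once a week* to frequency, and *no exercise* to type, intensity and duration.
- State that no exercise in the three-month window counts as non-adherence in the primary measure, and that these patients stay in the intention-to-treat analysis. The article defines no adherence score, so this rule must be written in the terms of the primary measure finally used.
- Make the duration bands mutually exclusive (for example 0–9, 10–19, 20–29, 30–44, 45–59, 60–89, 90–119, 120 or more, with *no exercise* as its own category), or record minutes and band them centrally.
- Code prescribed and reported values by the same written rule.

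The cost is a revised one-page form. If enrolment has begun, add a form-version flag to the data. If the full questionnaire already has such an answer or rule, it is enough to print it with Table 4 and correct the bands.

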### Secondary outcome measures

*Secondary outcomes* include anthropometry (body mass index, weight to height ratio), performance of leisure time physical activities, parameters of medical comorbidities (classification/severity) and clinical characteristics of the participants (systolic and diastolic pressure; blood total and low-density lipoprotein cholesterol concentration; fasting glycaemia; resting and peak heart rate during exercise testing; and peak oxygen uptake capacity).

*Anthropometry* Body mass index will be calculated (weight/(height)^2^) based on body height (m) and weight (kg) determined by a stadiometer and calibrated electronic scale, respectively. Waist-to-height ratio will be calculated by a standard formula (waist circumference/height), based on body height and waist circumference (cm) measured using a non-elastic tape measure at the narrowest point between the last rib and the iliac crest at the end of a normal expiration.

*Leisure time physical activities* To measure the prevalence of PA unqualified as sport-related or performance-oriented exercises (gardening, yard work, housework, carrying for another, home repairs) we will measure leisure time behaviours of participants via International Physical Activity Questionnaire – Short Form (IPAQ-SF). The IPAQ-SF is a validated and reliable questionnaire for assessment of frequency (days per week) and time (minutes per day) of PA realized during a past 7 days recall period in five domains: work, transportation, garden or yard, home, and leisure time [55]. The original English IPAQ-SF version was translated and cross-culturally adapted in several steps according to methodology established and described by the IPAQ developers group [http://www.ipaq.ki.se]. The Slovak IPAQ-SF version was subsequently reviewed by an expert and pre-tested [56, 57].

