### Procedure

Assessments will be conducted at two time points – (prior to patient’s behavioural consultation and 3 months follow-up the consultation). Completion of measurements should take maximally 30 min. One member of the investigatory team (AZ) will perform all measures in the trial. A dedicated member will undergo a training session to ensure consistency of assessment protocol and validity and reliability of applied diagnostics instruments.

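### The secondary outcome meant to capture activity other than exercise uses a questionnaire that, as described, also records exercise

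*Protocol article*

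**What the plan says.** The Secondary outcome measures section describes one outcome in three ways.

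- **Name.** The list of secondary outcomes calls it "performance of leisure time physical activities".
- **Purpose.** The paragraph on it opens: "To measure the prevalence of PA unqualified as sport-related or performance-oriented exercises (gardening, yard work, housework, carrying for another, home repairs". The target is therefore activity other than sport or training.
- **Instrument.** The same sentence continues: "we will measure leisure time behaviours of participants via International Physical Activity Questionnaire", short form. The next sentence says that the form records days per week and minutes per day of "PA realized during a past 7 days recall period", and gives its coverage as "in five domains: work, transportation, garden or yard, home, and leisure time".

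Two other places bear on this. Table 4, under Primary outcome measures, counts "Endurance training (walking, bicycling, swimming" as a type of exercise. The Procedure section states: "Assessments will be conducted at two time points", one before the consultation and one at 3 months. Table 1 schedules the physical activity questionnaire at both.

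**The concern.** The stated purpose and the stated instrument do not match. The outcome is meant to leave exercise out, but the questionnaire as described includes a leisure-time domain, where exercise taken in free time would naturally be reported. It also includes transportation, where some walking or cycling used as training could be reported. No sentence says that such activity is removed.

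This matters because the trial tests an exercise prescription and the second questionnaire is completed after it. If the digital prescription leads patients to exercise more than usual advice does, that exercise can appear as a group difference on an outcome presented as non-exercise activity. A reader would then conclude that patients also became more active around the house and garden when they may not have. The opposite question, whether patients give up everyday activity to make room for exercise, is one that the stated construct could answer, but an unrestricted score may not.

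**Working it through.** The article gives no figure to reproduce, and the check needs no arithmetic. It compares the stated purpose with the stated coverage, domain by domain, and then goes through the possible scorings.

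**Domains against purpose**

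| Domain as described | Fits the purpose (activity other than exercise)? | Can it hold exercise of the Table 4 kind? |
|---|---|---|
| Garden or yard | Yes, among the listed examples | Not ordinarily |
| Home | Yes, among the listed examples | Not ordinarily |
| Work | Broadly yes, though not a listed example and not leisure | Not ordinarily |
| Transportation | Mostly yes, though not a listed example | Possibly, if walking or cycling to a destination serves as training |
| Leisure time | Only in part | Yes: free-time walking, bicycling, swimming |

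The description lists garden/yard and home separately from leisure time. The tasks that define the purpose therefore sit outside the domain that shares the outcome's name.

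**Possible scorings**

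1. All five domains: exercise reported under leisure time, and possibly transportation, enters the score.
2. Leisure time only, as the name suggests: free-time exercise enters, and the garden and home tasks that define the purpose drop out.
3. Garden/yard and home only: this matches the listed examples, but the article does not say it and the outcome's name points elsewhere.
4. All domains except leisure time: this comes close to a broad reading of the purpose, but it is also not stated and contradicts the name.

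Exercise is recorded under the first two and largely avoided under the last two. The article does not choose.

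**What a single total would show.** Let E be a patient's change in exercise minutes per week and N the change in non-exercise minutes per week, between baseline and 3 months. A summed score changes by E + N. The stated construct is N alone. If E is positive and N is zero, the score rises by E with no change in the construct. If E is positive and N is negative, the score falls by less than the construct does, stays level (when E = −N) or rises. This holds only if a total is used. With domains reported separately, E and N could largely be told apart.

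**Size.** The article gives no value for E or N in either arm and no scoring rule, so the overlap cannot be computed. The control group also receives advice on physical activity, so what would contaminate the group comparison is the between-arm difference in E, which is not known either.

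**The case against.** The best case for the protocol has five parts.

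- **No scoring rule is stated.** The domain sentence describes what the questionnaire covers, not the analysed endpoint. Which domains are scored may be set out in a full protocol or analysis plan that is not shown. This stands as a limit: a reader might infer that prescribed exercise definitely is counted as non-exercise activity, but the article does not say so. It does not remove the point, because purpose and instrument are both stated and do not agree.
- **The listed tasks may be examples only.** Work and most transport activity are not sport. A reader might infer that three of the five domains lie outside the purpose, but the text does not support that count. Leisure time clearly admits exercise, and transportation does so in part.
- **The primary outcome is a different quantity.** A reader might infer that this outcome is the primary outcome counted again. It is not. The primary outcome is agreement between reported and prescribed type, duration, intensity and frequency over 3 months; the questionnaire records days and minutes over 7 days. A patient who exercises beyond the prescription could have more minutes and poorer agreement.
- **Masking needs a total.** A reader might infer that gains in exercise and losses in gardening must cancel. That assumes a summed score, which the article does not mention.
- **Little depends on this outcome.** It is one of many secondary measures and appears in neither stated aim, nor the hypothesis, nor the sample size. The randomised comparison of the questionnaire scores remains valid. The Table 4 questionnaire records exercise separately and would help with interpretation.

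These arguments make the consequence conditional and lower its weight. They do not make the instrument, as described, isolate the stated construct.

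**Conclusion.** The point holds in a limited form. As described, the instrument does not isolate activity other than exercise, and nothing in the article excludes exercise from it. Unless scoring is restricted, exercise taken up after the prescription can raise this outcome, and a group difference could not be read as a change in non-exercise activity. Masking of a fall in household or garden activity is a further risk only if a single total is used.

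The conclusion rests on two assumptions: that patients report free-time exercise under leisure time, as the domain names suggest, and that no unshown rule removes it. Whether the short form gives separate domain scores cannot be settled from the article. The size of the effect cannot be computed.

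Severity is minor. What is at stake is the meaning of one secondary outcome, not the validity of the comparison. The primary analysis and the sample size are untouched.

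**What to change.** Make the outcome's name, content and scoring agree, in one of two ways.

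1. **Keep the non-exercise construct.** State that only the garden/yard and home domains are scored, at baseline and at 3 months, and replace the leisure-time label with one that fits. This is possible only if the form used gives separate domain scores.
2. **Keep the whole questionnaire.** Rename the outcome *total physical activity, past 7 days*, drop the claim that it measures activity other than exercise, and state that it includes the prescribed exercise and so is related to, but not the same as, the primary outcome.

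The second needs only wording and no new data. The first needs no new data if the domains are recorded separately. The price in either case is a narrower claim for one secondary outcome.

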### Background measures

*Clinical data* included a list of patient’s CVD, CVD risk factors, other chronic non-cardiovascular co-morbidities, patient’s medication, systolic and diastolic blood pressure, blood total and low-density lipoprotein cholesterol concentration, fasting glycaemia, resting, and known patient’s adverse events registered during exercise testing. These data will be collected and reported by patient’s cardiologist and transferred from the patient’s medical record to the study file.

*The Health literacy* (HL) level will be assessed using The Health Literacy Questionnaire (HLQ) [58, 59]. This questionnaire comprises nine domains to provide a detailed profile of HL of populations, groups or patients of interest. The HLQ is divided into two parts which differ in response categories. Part 1 (domains 1–5) has 4 response categories rating the extent of agreement from 1 to 4. Part 2 (domains 6–9) has 5 response categories rating the level of difficulty from cannot do or always difficult (1), to always easy (5). Each domain was scored as the average of the item scores. The score ranges from 1 to 4 or 1 to 5 respectively, a higher score indicating higher level of health literacy. Cronbachs alpha in an earlier Slovak sample ranged from 0.73 to 0.84 among 9 HLQ domains [59].

Also, *lifestyle variables* and *socio-demographic data* will be collected via questionnaire developed for this study. The participants will provide standard information about age, education completed, marital status, number and age of descendants, living and work conditions and history, drinking and smoking habits.

